### Measurements

Attendance and attrition rates will be recorded. Various measures of sleep, mood, daytime functioning, quality of life, social support, and other factors will be assessed, either through online questionnaires *via* Qualtrics software (Qualtrics, 2018–2020) or hard copies posted to participants, to measure preliminary efficacy (Table 4). Participants will be asked whether they are completing the questionnaires for themselves, or, for caregivers, on behalf of the person they care for at the start of each questionnaire. The post-intervention (T2) questionnaire will gather quantitative/qualitative feedback on intervention helpfulness and usefulness, and assess the preliminary efficacy based on secondary outcomes. The 10-week follow-up (T3) will assess only secondary outcomes.

**Table 4 table-4:** Timing of measurements.

	Enrolment	Allocation	Post-allocation		
**Timepoint**	-t1	t0	T1	T2	T3
			**Week 0**	**Week 6**	**Week 10**
Enrolment	X				
Informed consent/assent Screening	X				
Allocation		X			
Intervention				
ASSESSMENTS					
Primary Outcome (Feasibility)					
Percentage of sessions attended by caregivers				X	
Drop-out rate				X	
Client Satisfaction Questionnaire				X	
Secondary Outcomes (Preliminary Efficacy)					
Pittsburgh Sleep Quality Index	X		X	X	X
Sleep Disturbance Inventory^a^	X		X	X	X
Insomnia Severity Index			X	X	X
PROMIS Sleep Related Impairment –SF			X	X	X
PROMIS Anxiety –SF			X	X	X
PROMIS Depression –SF			X	X	X
Depression, Anxiety and Stress Scales			X	X	
Health Questionnaire (EQ-5D-5L)^a^			X	X	X
The Alzheimer’s Disease-related Quality of Life scale^b^			X	X	X
Actigraphy^c^ • Sleep onset latency (mins) • Sleep efficiency (%) • Total sleep time (mins) • Wake after sleep onset (mins)		X		X	
Other Factors					
Demographics	X		X	X	X
Consensus Sleep Diary • Sleep onset latency • Sleep efficiency • Total sleep time • Number of overnight awakenings		X		X	
Reduced Morningness-Eveningness Questionnaire			X	X	X
PROMIS Emotional Support –SF –4a			X	X	X
PROMIS Instrumental Support –SF –4a			X	X	X
Intervention adherence and helpfulness				X	X
Adverse events				X	X
Credibility Expectancy Questionnaire			X		

**Notes.**

T0 Pre-study screening/consent and baseline

T1 Time-point 1 (Week 0) pre-intervention baseline questionnaire undertaken within one week of intervention start

T2 time-point 2 (Week 6) post-intervention

T3 Time-point 3 (Week 10) follow-up

X Undertaken at that time point

SF Short form

a Completed by caregivers only.

b Completed by persons living with dementia only.

c Actigraphy and sleep diary assessed for two weeks from pre-intervention to the start of Week 1, then from Week 5 to Week 6 (final two weeks of intervention).

#### Primary outcome

Feasibility will be assessed using domains outlined by Bowen et al. (2009). Implementation will be assessed by program adherence (defined as the number of sessions attended) and drop-out rate. Acceptability will be assessed *via* self-report of the overall program satisfaction and perceived benefit using the Client Satisfaction Questionnaire at post-intervention (CSQ; Attkisson & Zwick, 1982) and responses from the post-study evaluation survey. Limited efficacy will be assessed through measures outlined below.

#### Secondary outcomes

 1.*Sleep quality* measured by the PSQI, which has adequate reliability and validity in community samples with an internal consistency of *α* =.83 (Buysse et al., 1989). 2.*Sleep disturbance in people living with dementia* measured *via* the SDI. The SDI consists of seven items from the Neuropsychiatric Inventory sleep disturbance subsection (Cummings, 2020). Caregivers are asked to rate the frequency, severity and levels of caregiver distress associated with sleep-related behaviours displayed by the person in their care. 3.*Insomnia* symptoms measured by the Insomnia Severity Index (Bastien, Vallières & Morin, 2001). The ISI is a 7-item measure of self-reported insomnia symptoms. The ISI has been shown to have high internal consistency and a cutoff score of ≥8 has a sensitivity 96%–99% and specificity of 78%–92% in community and clinical populations respectively (Morin et al., 2011). 4.*Sleep-related daytime impairment* measured by PROMIS Sleep Related Impairment–Short Form–8a (PROMIS-SRI; Yu et al., 2011). 5.*Mood* measured by PROMIS Depression–Short Form–8a and PROMIS Anxiety–Short Form–8a (Pilkonis et al., 2011), both 8-item measures of depression and anxiety symptoms respectively, and the Depression, Anxiety and Stress Scales (Lovibond & Lovibond, 1995). 6.*Quality of life* measured by the EQ-5D-5L (Herdman et al., 2011) for caregivers and the Alzheimer’s Disease-related Quality of Life scale (Rabins et al., 1999) for people living with dementia. 7.*Objective sleep* measured *via* actigraphy. The actigraph (Actiwatch 2, Philips Respironics) is a small wrist-worn device resembling a wristwatch that incorporates an accelerometer, which detects body movement or lack of movement. Actigraphy data will be collected in conjunction with information from sleep diaries. An algorithm is then used to infer various sleep outcomes (*e.g.*, sleep onset, duration, time in bed) based on the absence of recorded movement. Although actigraphy does not measure sleep itself, the current algorithm of analyses made by these devices can provide feasible and valuable information about insomnia-related parameters and information related to circadian sleep-wake patterns that polysomnography is unable to provide (Krystal & Edinger, 2008). Actigraphy was verified using the Consensus Sleep Diary (Carney et al., 2012). Parameters used in the current study include: sleep onset latency in minutes, percentage of sleep efficiency, total sleep time in minutes, and wake after sleep onset in minutes.

### Other factors

 1.*Demographic* information such as medical or mental health conditions, details on dementia diagnosis, living arrangements, medication use and engagement in other therapies. 2.Amount of daily *light exposure*, *daytime naps* and *physical activity* in minutes assessed through additional questions in the adapted sleep diary. 3.*Chronotype* assessed *via* Reduced Morningness-Eveningness Questionnaire (Adan & Almirall, 1991). 4.*Social support* measured using four item scales: PROMIS Instrumental Support–Short Form–4a and PROMIS Emotional Support–Short Form–4a (Hahn et al., 2014). PROMIS Instrumental Support has been used among caregivers and yields a high internal consistency of *α* =.90 (Kent et al., 2020). 5.*Intervention adherence and helpfulness* will be assessed through rated frequency of use and helpfulness of various strategies (*e.g.*, practical sleep strategies, relaxation strategies, physical activity, guidance on light exposure, enlisting social support) through questions developed by the research team. Qualitative feedback will also be obtained. 6.*Adverse events* are assessed formally through questions developed by the research team. 7.*Credibility and expectancy of treatment* is assessed *via* the Credibility Expectancy Questionnaire (Devilly & Borkovec, 2000).

### Adverse events

Risks of participation are minimal and may include skin irritation caused by the actigraph band and psychological discomfort in completing questionnaires. Side-effects of participation will be formally assessed in the post-intervention and follow-up questionnaires. Any adverse events that occur throughout the trial will be recorded. Participants may discontinue actigraph use or completing questionnaires in the event of discomfort, and will be asked to communicate this to researchers. Participants will be encouraged to speak to their doctor in the event of ongoing poor sleep beyond completion of the trial and will be provided with details the following support services: National Dementia Helpline, Dementia Australia Counselling, Beyond Blue and Lifeline.

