#### Intervention

After screening, eligible participant dyads will participate in a 20-minute “pre-orientation” session *via* video with a trained research assistant to explain use of actigraph and sleep diary, which are sent *via* post prior to predetermined start date. Participants will complete an online baseline questionnaire within a week prior to beginning the intervention; automatic prompts to complete all items will be provided, and email reminders will be sent if questionnaires have not been completed within five days of release*.* Eligible participants will receive the intervention as detailed below. Participants will wear an actigraph and complete sleep diaries daily for two weeks prior to intervention start date, and then return the watches and diaries to the research team to be downloaded and recharged. The actigraphs and new diaries will be posted to be worn again during Weeks 5 and 6 of the intervention. A trained research assistant will manage actigraph recharging and monitor data. Sleep diaries and actigraphs are returned following completion of the follow-up questionnaire (Week 10). Ethics approval will be sought by Monash University Human Research Ethics Committee for any protocol modifications before being implemented and communicated to participants if appropriate, and will be documented on a running sheet.

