Group sessions will generally include: (a) an initial review of the previous session and time to answer questions; (b) psychoeducation of key concepts and strategies specific to each session and; (c) guided discussion to enable sharing and collaboration, and reference to relevant sections of the workbook. The purpose of Session 4 is to provide a personalised check-in to encourage engagement and adherence, answer any questions and collaborate a plan for the remaining period of intervention.

**Table 3 table-3:** Outline of personalised and group sessions.

**Session 1**	**Introduction (Individual dyads)**
	Acknowledgement of Country Overview of project Psychoeducation: • Typical sleep changes in people living with dementia and caregivers • Sleep deprivation vs insomnia • “3 ingredients for good sleep”—sleep drive, circadian rhythm, quiet mind Cognitive behavioural strategies for insomnia: • Stimulus control (*e.g.*, only going to bed when sleepy, getting out of bed if stimulated and unable to sleep) • Anchoring wake time • Guidance on napping • Sleep hygiene Collaborative goal-setting, motivational interviewing, personalising strategies Workbook exercises
**Session 2**	**Light, Night and Exercise (Group Session)**
	Introduction (including Acknowledgement of Country, group guidelines) Psychoeducation: • Circadian rhythm and sundowning • Role of light and exercise on circadian rhythms (including blue light) • Effect of light at different times of day/night Light therapy strategies: • Natural light exposure upon awakening and during daytime • Avoidance of bright lights at night (using lamps, dim lights) • Guidelines on electronic device use Psychoeducation: • Exercise and sleep, physical and mental health Encouraging physical activity (*i.e.,* 30 min of physical activity a day) Group discussion (implementing light and night strategies into daily routine) Workbook exercises
**Session 3**	**Self-care and Relaxation (Group Session)**

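### Adverse-event questions are scheduled only at T2 and T3, with no stated active question for dyads who leave the sessions, so harms linked to drop-out may be under-ascertained

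*Protocol article*

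**What the plan says.** The Adverse events section of the protocol article makes three statements that bear on how harms are found.

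- Scheduled assessment: "Side-effects of participation will be formally assessed in the post-intervention and follow-up questionnaires". Table 4 matches this, with the adverse-events row marked at T2 and T3 and nowhere else. The Other factors list says of adverse events that they "are assessed formally through questions developed by the research team".
- Ongoing recording: "Any adverse events that occur throughout the trial will be recorded".
- Stopping a study procedure: "Participants may discontinue actigraph use or completing questionnaires in the event of discomfort, and will be asked to communicate this to researchers".

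Drop-out is itself part of the primary outcome. Implementation is judged by "program adherence (defined as the number of sessions attended) and drop-out rate". The article describes no exit contact and no question about the reason for leaving.

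The text on T3 is not consistent. The Measurements section limits the Week 10 follow-up to the secondary outcomes. Table 4 places adverse events under Other Factors, not under the secondary outcomes, and still marks them at T3. The Adverse events section also assesses side-effects at follow-up.

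**The concern.** A promise to record events is not the same as a plan to ask about them. As written, events are solicited twice, both times by questionnaire, at or after the end of the intervention. Anything else reaches the data only if a participant volunteers it or a therapist happens to hear of it.

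That matters most for dyads who leave. If some leave because the programme disagreed with them, and those dyads are also less likely to return the later questionnaires, the count of harms is incomplete in the group where harms are most likely. The trial is meant to inform a larger randomised trial in people with dementia and their caregivers, and a tolerability summary based mainly on those who stayed would be a weaker guide than it need be. Drop-out is also harder to interpret as a feasibility outcome if nobody has asked why dyads left.

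**Working it through.** The plan has no harm rate, expected drop-out or power calculation to reproduce; 24 dyads is a convenience sample. The check is therefore mainly a reading of the text.

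**Step 1: which routes exist, and whom do they reach?**

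| Route stated in the article | Active question? | Reaches a dyad that leaves the sessions? |
|---|---|---|
| T2 and T3 questionnaires | Yes | Only if it still answers; the article does not say whether such dyads are sent them |
| Recording of any event during the trial | No, recording only | Only if the event is volunteered or noticed |
| Request to report discomfort on stopping the actigraph or questionnaires | A request tied to those two procedures | Leaving the sessions is not named |
| Email reminders | Not applicable | Stated alongside the baseline questionnaire: "email reminders will be sent if questionnaires have not been completed within five days of release" |

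No row gives an active adverse-event question between the start of the intervention and T2, or at withdrawal from the sessions.

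**Step 2: are the statements compatible?** Yes. Scheduled solicitation at two points and continuous recording of whatever is reported can stand together. The weakness is in how completely events are found.

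**Step 3: how many dyads could be affected?** Drop-out is not given, so I assume 10% to 30%, and I also assume that dyads that drop out answer neither T2 nor T3.

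- 24 × 0.10 = 2.4, about 2 dyads
- 24 × 0.30 = 7.2, about 7 dyads

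**Step 4: what would that leave unknown?** Suppose none of the responding dyads reports an event and nothing is volunteered by the others. The number of dyads in the sample with an event could then be anything from zero up to the number not asked:

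- 2 not asked: 0 to 2/24 = 8.3%
- 7 not asked: 0 to 7/24 = 29.2%

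These are limits on what the data could exclude under the assumptions. They are not estimates of harm or of bias.

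**Step 5: is T3 secure as a second point?** Taken literally, the Measurements sentence restricting T3 to secondary outcomes would leave T2 as the only formal adverse-event assessment. Table 4 and the Adverse events section both point the other way, so T3 is very probably intended, but the wording should agree.

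**The case against.** The strongest reply is that the plan provides for more than two questionnaires. It promises ongoing recording and asks people who stop the actigraph or questionnaires for discomfort to say so. Psychologists meet attending dyads weekly from manualised scripts that are not shown, and Session 4 reviews changes in sleep and wellbeing with each dyad individually. Leaving the sessions need not mean ignoring a questionnaire, and the voucher depends on the final questionnaire and return of the actigraph and diary, not on attendance. A withdrawal procedure may sit in the full protocol.

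Much of this stands, and it rules out several stronger readings that a reader might infer:

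- **That dyads who leave are never asked about harm.** The article does not say that they are excluded from T2 or T3. It does not say that they are included either.
- **That the promise to record all events contradicts the schedule.** It does not; see Step 2.
- **That the plan treats only the device and questionnaires as sources of risk.** The text reads "Risks of participation are minimal and may include skin irritation caused by the actigraph band" and goes on to questionnaire discomfort. That wording is open-ended, so advice such as "getting out of bed if stimulated and unable to sleep" cannot be said to have been ruled out as a source of harm.
- **That a biased harm rate would decide whether a larger trial follows.** Feasibility rests on attendance, drop-out and satisfaction. Adverse events are listed under other factors, and no harm rate is a progression criterion.
- **That the bias can be sized.** One can suppose that 4 of 24 dyads have an event (16.7%) and that 3 of them leave, so that the questionnaires show 1 of 21 (4.8%). Those inputs are invented, and nothing in the article supports them.

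What remains is that the article explicitly fixes when and how adverse events are formally sought. That is a stated schedule, not a detail lost in condensing, and none of the other routes is a standard question put to every dyad.

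**Conclusion.** The point holds as a limited weakness in ascertainment. Systematic adverse-event questions are fixed at T2 and T3 only. No active question is stated during the six intervention weeks or for dyads that leave the sessions. Harms in dyads that drop out and answer neither questionnaire may therefore be under-ascertained.

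The scale, about 2 to 7 of 24 dyads, rests on an assumed drop-out of 10% to 30% and on non-response by those dyads. If they are in fact sent T2 and T3 and reply, the gap shrinks to later recall in place of prompt enquiry. The direction, towards too few events, is plausible; its size cannot be derived from the article. Separately, the description of T3 needs reconciling.

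**What to change.** In the Adverse events section and Table 4:

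1. Add one standard adverse-event question, covering both the caregiver and the person with dementia, at Session 4, which is already an individual contact. Around the group sessions, ask it privately where practicable, since up to four dyads share those sessions and Session 5 is for caregivers only.
2. Ask the same question at any withdrawal contact, together with the reason for leaving, and state whether dyads that leave the sessions are still sent T2 and T3.
3. Report events over all dyads that started Session 1, separating solicited from spontaneously reported events.
4. Record the date of the change. Recruitment began in May 2022 and data collection was ongoing, so some dyads will have been followed under the existing schedule.
5. Reword the Measurements sentence on T3 so that it agrees with Table 4 and the Adverse events section.

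The cost is a little session time and a minor amendment, for which the article already describes an ethics route. The downsides are mixed ascertainment before and after the change, in a sample of only 24 dyads, and possibly a higher reported event rate because people are being asked. Separating solicited from spontaneous events and dating the change make both visible to a reader.

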### Reimbursement

Participants will receive an $100 electronic gift voucher upon completion of the final questionnaire and return of actigraph and sleep diary. Participants are provided with a comprehensive list of relevant support services for ongoing support.

### Trial status

The project began recruiting in May 2022 and data collection is ongoing.

## Data Analysis

### Sample size

Given the feasibility nature of this study, a convenience sample of 24 dyads will be recruited; no power analysis was conducted.

### Data storage and management

All data will be stored under password protection. A tracking sheet contains personal details will be stored separately from responses to screening questions and questionnaires. Participants will be assigned a unique code to link responses across time-points. Interim data will only be accessible by investigators and research assistants involved in data collection and analysis; lead investigators and research assistants will have access to the final dataset. Identifiable data will be kept for seven years following any publications and thereafter destroyed. To promote data quality, data will be screened for accuracy and further enquiries will be made by research assistants and rectified.

Participants may request further clarification of questionnaire items; help will be provided by research assistants *via* telephone/email. A data monitoring committee will not be employed due to limited scale, and auditing will not be undertaken. The trial will be terminated upon achievement of recruitment target.

### Statistical analysis

Descriptive data will be presented as means and standard deviation, or percentages where appropriate. Feasibility will be assessed *via* percentage of sessions attended, drop-out rate, and scores of 75% or more on the CSQ at post-intervention for caregivers. Changes in PSQI, ISI and SDI scores, actigraphy-assessed sleep (*i.e.,* sleep efficiency, sleep onset latency, wake after sleep onset, total sleep time), DASS, PROMIS Depression/Anxiety, EQ-5D-5L and Alzheimer’s Disease-related Quality of Life Scale, and PROMIS Emotional/Instrumental Support scores from T1 to T3 will be assessed using linear mixed models, controlling for age and gender. Cohen’s *d* will be used to estimate effect sizes.

### Dissemination

Results will be disseminated through peer-reviewed publications and conferences. Findings may also be disseminated through relevant organisations, support groups and media (including social media) outlets. Participants who elect to receive the results of the study will be contacted upon trial completion with a brief summary of findings. Those who have contributed significantly to the development, conduct, analysis and reporting of the trial will be granted authorship for any arising publications involving trial data. Authors may be contacted for requests on accessing materials, data and code.

## Discussion

Over 91% community-dwelling people with dementia are supported by a caregiver at home (Brooks, Ross & Beattie, 2015), and in this population, sleep disturbances remain prevalent and are related to a range of undesirable outcomes. The prevalence of dementia is anticipated to rise steeply over coming decades, which will place significant demands on caregivers and dementia-related healthcare services (Standfield, Comans & Scuffham, 2018). Therefore, effective, feasible interventions that promote sleep health and wellbeing in caregivers are much needed to support people in their caregiving roles.

Existing sleep interventions commonly address sleep concerns in persons with dementia and caregivers separately (Pignatiello et al., 2022; O’Caoimh et al., 2019). Our intervention offers a novel approach by concurrently targeting sleep concerns in dyads of caregivers and care-recipients through multiple modalities in an attempt to more comprehensively and collaboratively address dyadic sleep disturbance. From a cognitive behavioural perspective, *perpetuating* factors of sleep disturbance are targeted, for example, caregivers may learn strategies to support their own healthy sleep practices and sleep health in the person they support which may contribute to their experience of sleep disturbance.

A strength of our trial was the engagement of lived experience perspectives in the design and development of the intervention. We engaged consumer and community perspectives (*i.e.,* through focus groups, interviews, questionnaires and iterative reviews of processes and materials from community advisors) in the development of this intervention and combined components from existing evidence-based interventions targeting caregivers and people living with dementia in an attempt to better meet the needs of the community. Additionally, the online and group-based delivery of the intervention aims to increase accessibility and timeliness of care to dyads experiencing poor sleep who may not otherwise be able to visit a clinician; thus improving health equity. This also allows for a much higher treatment frequency at a lower time cost, which may have a positive impact on individual compliance and ultimately on overall intervention success.

The feasibility nature of our trial will provide proof-of-concept data and limited-efficacy testing to support a larger-scale effectiveness-implementation trial. Results from our study will allow us to evaluate who may be better suited to this intervention (*e.g.*, people living with certain types of dementia, or dyads with certain types of sleep disturbance), as well as other considerations (*e.g.*, whether proxy or self-report assessments should be used) in future larger evaluation trials. Some limitations of the trial include: lack of specific assessment of dementia stage (*i.e.,* mild, moderate, severe) and subtype, which can contribute to nocturnal sleep disturbances; lack of assessment of whether participants completed past sleep studies and their results; online assessments which older adults may find challenging; and flexibility in questionnaire respondents (*i.e.,* some caregivers may complete questionnaires on behalf of the person they support which may risk bias).

If feasible and effective upon further testing, this intervention could represent an accessible, low-cost way of reducing sleep disturbance and negative daytime effects in dyads of co-residing caregivers and the people living with dementia in the community which may hold larger-scale societal and economic implications in the promotion of sleep and wellbeing in dementia and caregiving communities.

